# The effectiveness of a modified Gui Zhi Fu Ling Wan formulation (Gynoclear™) for the treatment of endometriosis: a study protocol for a placebo-controlled, double-blind, randomised controlled trial

**DOI:** 10.1186/s13063-021-05265-x

**Published:** 2021-04-21

**Keywords:** Endometriosis, Gynoclear, Chinese herbal medicine, Pelvic pain

## Abstract

**Background:**

Endometriosis is the presence of tissue similar to that of the endometrium outside the uterine cavity and is the most common cause of chronic pelvic pain. Current non-surgical treatments such as non-steroidal anti-inflammatories, oral contraceptive pills and hormonal treatments have limited effectiveness, and the side effect profile is bothersome. This study will evaluate the efficacy of Gynoclear™ by change in endometriosis-related pain based on the Endometriosis Pain Daily Diary (EPPD) scores.

**Methods:**

This randomised, double-blind, placebo-controlled trial will recruit a minimum of 90 adult participants across Australia who have a laparoscopic visualisation/confirmation of endometriosis in the last 5 years and have current moderate or greater pelvic pain. Participants will be randomly allocated in a 1:1 ratio to receive either Gynoclear™ (active) or placebo. Gyncolear’s active ingredients are *Carthamus tinctorius* (Safflower), *Cinnamomum cassia* (Chinese cinnamon), *Poria cocos* (Hoelen), *Paeonia suffriticosa* (Tree peony), *Paeonia lactiflora* (Peony) and *Salvia miltiorrhiza* (Red sage). Participants are asked to complete a total of 5 months’ worth of pain diary entries via the EPDD v3, including 1-month screening, 2-month treatment period and 1-month post-treatment follow-up. The primary outcome variable is change in endometriosis-related pain based on the EPDD v3 scores. Secondary outcomes include change in health-related quality of life via the Endometriosis Health Profile (EHP-30), SF-12 and EQ-5D scores as well as changes in rescue analgesic usage, dyspareunia and fatigue via the EPDD.

**Discussion:**

This study will determine the safety and efficacy of Gynoclear™ to reduce the severity and duration of non-cyclical pelvic pain, dysmenorrhoea, dyspareunia and other symptoms of endometriosis. Study outcomes will be of interest to health professionals and members of the public who suffer from endometriosis.

**Trial registration:**

Australia and New Zealand Clinical Trials Registry ACTRN12619000807156. Registered on 3 June 2019.

**Supplementary Information:**

The online version contains supplementary material available at 10.1186/s13063-021-05265-x.

## Background

Chronic pelvic pain (CPP) is pain in the pelvis of greater than 6 months duration, which is severe enough to cause functional disability or require medical intervention [1]. Chronic pelvic pain has a number of aetiologies including endometriosis, adenomyosis, chronic pelvic infection and functional disorders such as irritable bowel syndrome or interstitial cystitis. Endometriosis is the presence of tissue similar to that of the endometrium outside the uterine cavity [2] and is the most common cause of CPP [3].

Worldwide prevalence rates of all types of chronic pelvic pain range from 5.7 to 26.6% [4]. Accurate prevalence rates for endometriosis are difficult to estimate. Reports from clinical settings suggest a rate of around 10% globally [5], and in Australia, around 11% of women aged 40–44 have a diagnosis of endometriosis [6].

Current non-surgical treatments such as non-steroidal anti-inflammatories, oral contraceptive pills and hormonal treatments have limited effectiveness [7], and the side effect profile is bothersome, with discontinuation rates of between 25 and 50% [8]. These factors may contribute to the observation that non-pharmacological self-care use is very common with 75% of Australian women with endometriosis reporting using self-care in the past 6 months. Sixteen percent of these women were using herbal medicine to help manage their endometriosis symptoms or the side effects of their conventional medications [9].

Gui Zhi Fu Ling Wan (GZFLW), a traditional Chinese medicine (TCM), has been used for gynaecological disorders since the fifteenth century [10]. Gui Zhu Fu Ling Wan consists of five herbs, Gui Zhi (*Ramulus cinnamomi*), Fu Ling (*Poria cocos*), Mu Dan Pi (*Cortex moutan radix*), Bai Shao (*Radix Paeoniae alba*) and Tao Ren (*Semen persicae*). The formulation is indicated for chronic pelvic pain, fibroids and severe dysmenorrhoea [11]. A modification of GZFLW, containing similar western herbal species and with the addition of another herb Dan Shen (*Salvia miltiorrhiza*) and the substitution of Tao Ren for another similar herb Hong Hua (*Carthamus tinctorius*), has been used by our partners Metagenics to create Gynoclear™. This particular combination has not been scientifically evaluated for the treatment of endometriosis-related pain.

The aim of this study is to evaluate the efficacy and safety of Gynoclear™ on pelvic pain, fatigue and other quality of life measures in women with a confirmed diagnosis of endometriosis.

## Methods

A randomised, placebo-controlled, double-blind, clinical trial to evaluate the efficacy of a modified Gui Zhi Fu Ling Wan formulation (Gynoclear™) for the treatment of endometriosis-related pelvic pain. Australian ethics approval from Western Sydney University Human Research Ethics Committee, H13256 (approved May 2019). The trial was prospectively registered with the Australia New Zealand Clinical Trials Registry: ACTRN12619000807156. Recruitment began in June 2019 and is currently ongoing. Single centre study recruiting from all of Australia (NSW, VIC, WA, TAS, QLD and SA). Coordinating centre: NICM Health Research Institute at Western Sydney University, Penrith NSW 2751 Australia.

### Participants

Eligible participants are aged 18 to 45, have a laparoscopic visualisation/confirmation of endometriosis in the last 5 years, self-reported menstrual or non-menstrual pelvic pain and at least one of the common endometriosis-related forms of pelvic pain will be recruited. Full inclusion and exclusion criteria are presented in Table 1.

**Table 1 Tab1:** Inclusion and exclusion criteria

**Inclusion criteria:**	
Age 18–45 years.	
Laparoscopic visualisation/confirmation of endometriosis in the last 5 years.	
Have menstrual or non-menstrual pelvic pain rated ≥4/10 on a numeric rating scale based on an average over 1 month via endometriosis pain daily diary (version 3) scores.	
Report at least ONE of the following:	
Dysmenorrhoea (period pain),	
Dyspareunia (pain during or after sexual intercourse),	
Dyschezia (pain before or during bowel motion) OR	
Dysuria (pain prior to or during urination).	
Willing to provide informed consent and adhere to the protocol.	
Able to travel to a Laverty Pathology (or its sister companies) collection centre for two blood tests; one at baseline and the second at the end of the intervention approximately 12 weeks later	
If sexually active, agreeing to use appropriate contraception to prevent pregnancy during the study period.	
Has internet access (either via a mobile, tablet or computer) for completing the Endometriosis Pain Daily Diary v3 scores.	
**Exclusion criteria:**	
Have had endometriosis related surgery in the previous 6 months or have any surgery planned during the study period.	
Started or stopped/removed any hormonal contraceptive within the last 6 months. This includes the oral contraceptive pill (GnRH-a or danazol), implant contraceptives and the Mirena.	
Started, stopped or changed dosage on any pharmaceutical medication or herbal/natural medicine targeting endometriosis symptoms (such as pregabalin, Nortriptyline, or other Chinese herbal medicine) in the previous 6 months	
Having a known allergy or intolerance to any of the ingredients in Gynoclear™	
Participant has previously used Gynoclear™ for any condition.	
Participant is currently using a herbal supplement that contains any of the main constituents of the Gynoclear™ formula (e.g. Mediherb Endofem).	
Usage of anticoagulants (e.g. Warfarin, Heparin, Eliquis, Pradaxa, Xarelto) or any other medication, including nutritional and/or herbal supplements that may cause blood thinning (e.g. Vitamin E, *Gingko biloba*).	
History of coagulation disorders.	
Currently pregnant or breast feeding or planning on becoming pregnant during the study period.	

Based on a 20% difference in pain (measured by a 0–10 NRS) between groups (a moderate effect size *d* = 0.5 and a clinically significant difference), a standard deviation in pain scores of 2.2 (based on pilot data), an alpha of 0.05 and a power of 80% would mean 74 participants would need to be recruited. Given a predicted 20% drop out rate, 90 participants in total (45 per group) will be recruited. At the time of manuscript submission, 24 participants have been randomised.

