### Randomisation

After signing the informed consent document and satisfying the eligibility criteria, participants will be randomised in a 1:1 ratio to either the active treatment group (Gynoclear™) or the placebo control.

Using Castor EDC’s randomisation function, a randomisation sequence using a block size of 6, with 1:1 group allocation, was performed on the 15th of January 2019 by NICMs Clinical Trial Manager who is external to this study. Randomisation numbers were allocated in permuted blocks of 6 containing 3 active and 3 placebo randomisation numbers. The investigator will allocate each randomisation number in order of number sequence starting with the lowest number in each block and using all numbers in a block of 6 before starting with the lowest number in the next block of numbers. As soon as the randomisation number is assigned, it will be recorded on the participant log, in the patient notes and case report form. Details of any patients randomised out of sequence will be notified immediately to the Chief Investigator.

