### Analysis plan

All data is captured via Castor EDC digitally, there are no paper instruments used in this trial. Data will be exported from Castor EDC into SPSS v24 (or greater). Prior to analysis, data will be cleaned by examining frequencies, means, medians, and ranges to identify logical errors. Instruments will be coded according to their respective scoring instructions. Unless specified by the instrument, missing items will be imputed based on averaging values within the instrument for a given individual, if no more than 15% of items are missing. Otherwise, that instrument will be set to missing for the individual.

Baseline demographics will be reported using descriptive statistics. Daily pain scores (as measured by the EPDD) will be converted into a single pain score at five time points, baseline, month 1, month 2, trial exit/end of intervention and follow-up. This single pain score will be achieved by taking the mean of the daily pain scores for the previous 4 weeks. Both a per-protocol and intention to treat analysis will be undertaken for the primary outcome of changes in pain scores. The same process of generating a single score will be used for the following outcomes: pain interference with activities of daily living (0–10), use of analgesics (number of days per month needing additional medication), severity of fatigue (0–10) and severity of dyspareunia (0–10). All scores will be analysed using repeated measures at baseline, month 1, month 2, trial exit and follow-up via a longitudinal linear mixed model analysis of variance with time and group as fixed effects and subject as a random effect.

Secondary outcomes of changes in EHP-30 scores, SF-12 scores and EQ-5D scores will be analysed using analysis of variance between baseline and one-month follow-up. FSS scores will be analysed using paired analysis of variance between baseline and the end of the intervention. Baseline values with be used as covariates in the analysis.

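### The sample-size paragraph contradicts itself: its two statements of the effect need 128 or 42 evaluable women, the stated 74 matches neither, and 90 less 20% dropout leaves 72

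*Protocol article*

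**What the plan says.** All the inputs stand in one paragraph of the protocol article (Methods, Participants, after Table 1).

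- Effect: "Based on a 20% difference in pain (measured by a 0–10 NRS) between groups", glossed in brackets as "a moderate effect size *d* = 0.5 and a clinically significant difference".
- Spread: "a standard deviation in pain scores of 2.2 (based on pilot data").
- Error rates and result: "an alpha of 0.05 and a power of 80% would mean 74 participants would need to be recruited".
- Dropout: "Given a predicted 20% drop out rate, 90 participants in total (45 per group) will be recruited".

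The Randomisation section adds that "participants will be randomised in a 1:1 ratio". The Analysis plan reduces the daily scores to five four-weekly means (baseline, month 1, month 2, end of intervention, follow-up) and analyses them with "a longitudinal linear mixed model analysis of variance with time and group as fixed effects and subject as a random effect".

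The article does not give the sidedness of the test, a mean pain score to which 20% could refer, a correlation between time points, or the formula used.

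**The concern.** The paragraph presents 20% of a 0–10 scale and d = 0.5 as the same quantity. With the stated SD they differ almost twofold, and the stated total follows from neither under the usual two-group calculation. The dropout step then gives a number that does not preserve the total it starts from.

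The sample size is the trial's main claim about what it can detect. As written, a reader cannot tell which difference has 80% power. A null result could be taken as evidence against a moderate effect that the trial may or may not have been able to detect. A positive result cannot be set against a clearly stated clinically significant difference.

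**Working it through.** **Inputs.** Two-sided alpha 0.05 (sidedness is my assumption; one-sided is also shown), power 80%, SD 2.2, 1:1 allocation, 20% dropout, 90 recruited. All but the sidedness come from the article.

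**1. The two effect sizes.**
- d = 0.5 with SD 2.2: 0.5 × 2.2 = 1.1 points, or 11% of a 0–10 scale.
- 20% of a 0–10 scale: 2.0 points, and 2.0/2.2 = 0.91.

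**2. Trying to reproduce 74.** The normal approximation is n per arm = 2(1.960 + 0.842)²/d² = 15.70/d². The noncentral-t calculation is slightly larger and is the one used below.

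| Reading | d | Total, normal approx. | Total, t-test | One-sided, t-test |
|---|---|---|---|---|
| d = 0.5 (1.1 points) | 0.50 | 126 | 128 (63.8 per arm) | 102 |
| 2.0 points | 0.91 | 38 | 42 (20.002 per arm, rounded up to 21) | 32 |

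No entry is near 74. A paired t-test at d = 0.5, which would not fit a parallel-group trial, gives 34.

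If 20% means 20% of a mean score, the answer depends on a mean that the article does not give. For assumed means of 4 to 8, the difference is 0.8 to 1.6 points and the total runs from 240 down to 62. A total of 74 needs a mean of about 7.3 (0.2 × 7.3 = 1.46 points; 1.46/2.2 = 0.66), which again contradicts d = 0.5.

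**3. What 74 corresponds to.** With 37 per arm, 80% power is reached at d = 0.66, that is 0.66 × 2.2 = 1.45 points.

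**4. Dropout.**
- To keep 74 evaluable: 74/(1 − 0.20) = 92.5, so 93, or 94 in equal arms.
- From the stated 90: 90 × 0.80 = 72, or 36 per arm.
- Multiplying instead of dividing gives 74 × 1.20 = 88.8, close to 90. This may be how 90 arose, but the article does not say.

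**5. Power for an unadjusted two-sided comparison at one time point.**

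| Evaluable per arm | d = 0.5 | d = 0.91 |
|---|---|---|
| 36 (90 less 20%) | 55% | 97% |
| 37 (the stated 74) | 56% | 97% |
| 45 (no dropout) | 65% | 99% |

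With 36 per arm, 80% power is reached at d = 0.67, that is 0.67 × 2.2 = 1.47 points. One-sided power at d = 0.5 with 36 per arm is 68%.

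**6. Sensitivity to the planned analysis (all correlations r are assumptions).**
- One baseline and one end-of-treatment value, adjusted for baseline: variance factor 1 − r². With 72 women, power at d = 0.5 is 59%, 68% and 83% for r = 0.3, 0.5 and 0.7. About 80% needs r = √(1 − 72/128) = 0.66.
- Baseline-adjusted mean of m post-baseline values under equal correlations: variance factor (1 + (m − 1)r)/m − r². For m = 3 on-treatment months its maximum is 0.444 (at r = 1/3), so power at d = 0.5 with 36 per arm is at least 88% for every non-negative r.
- Repeated-measures F test of the group effect, five measurements, f = 0.25 (d = 0.5): N = 68, 74 and 78 for r = 0.40, 0.45 and 0.50.

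**The case against.** The strongest reply is that the protocol does not plan a t-test at one time point. It plans a mixed model over five time points, and such a model can be much more efficient. If the tested effect is the average over the three treatment months, 72 women have at least 88% power at d = 0.5 under equal correlations. A repeated-measures F test reaches exactly 74 at a correlation of 0.45. On this view nothing is miscalculated: a correlation was simply left out of a condensed article.

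Part of this stands. A reader might infer from the t-test figures that the trial's real power is about 55%, or that d = 0.5 can be rescued only if the baseline-to-outcome correlation is at least 0.66. The article supports neither as a general statement. Both hold for a comparison at a single time point, and the article does not say which contrast of the mixed model is primary. Nor does it settle the direction of the error: if 2 points was meant, 72 women give about 97% power.

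The reply does not repair the paragraph. The article mentions no correlation and no repeated-measures calculation, so 0.45 is a value chosen to fit. That F test also counts baseline as one of the five measurements, where no treatment effect can exist. No choice of correlation makes 2.0 points with SD 2.2 equal to d = 0.5.

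On dropout, the abstract calls 90 a minimum, the shortfall is only two women (about one percentage point of power at d = 0.5), and a mixed model can use the months that a dropout completed. The error is therefore small, but 90 less 20% is still below 74 under every reading of the effect.

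**Conclusion.** The point holds as an inconsistency in the stated derivation. The two descriptions of the effect are 1.1 and 2.0 points. For a two-group comparison at two-sided 0.05 and 80% power they need 128 and 42 evaluable women. The stated 74 fits neither and corresponds to about 1.45 points (d = 0.66), and the recruited 90 leaves 72 after the predicted dropout.

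These totals rest on a two-sided test, an SD of 2.2 and no gain from repeated measures or baseline adjustment. The power of the planned analysis remains open. At d = 0.5 with 72 evaluable it runs from about 55% (one time point, unadjusted) to 88% or more (baseline-adjusted average of three treatment months, equal correlations). A claim that the trial is underpowered goes further than the article allows. The claim that its sample-size figure cannot be derived from what it states does not.

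**What to change.** Keep 90 women and rewrite the paragraph so that it states:

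- the target difference in NRS points, replacing the 20% and reconciled with d and the SD of 2.2;
- the sidedness of the test;
- the contrast of the mixed model that is tested, for example end of treatment or the average over the treatment months;
- any correlation assumed, with its source in the pilot data;
- the power for that analysis.

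If the calculation rests on an unadjusted comparison at one time point, suitable wording is: *With 90 randomised and 72 evaluable, an unadjusted two-sided comparison at one time point has 80% power for a difference of about 1.5 points (d = 0.67, SD 2.2) and about 55% power for 1.1 points (d = 0.5).* If it rests on repeated measures or baseline adjustment, give the correlation and the resulting power instead. The 55% should not be written in without its condition.

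For dropout, either give 94 in equal arms as the number needed to keep 74, or keep 90 and state that 72 are expected to be evaluable.

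The cost is a rewritten paragraph. The stated power may become less favourable. With 90 kept, no extra participants are needed.

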### Patient and public involvement

Two streams of focus groups were conducted to co-design the trial with key stakeholders. The two groups were women diagnosed with endometriosis (*n* = 67) and TCM, herbalist or naturopathic practitioners (*n* = 8). These groups provided input on feasibility, dosage, outcome measures and duration of the trial.

### Recruitment and selection

Recruitment for this study is primarily via our partners Endometriosis Australia social media presence as well as paid Facebook advertising. All advertisements will advise participants of the trial and refer them to the Research Institute webpage. A link to a pre-screening survey will be available on the webpage to allow participants to self-screen against the inclusion and exclusion criteria of the study. All potentially eligible participants, based on their responses from the survey, will be instructed to schedule a call with the clinical trial officer or another member of the research team for follow-up procedures.

Potential participants will be required, after giving consent, to fill in a previously validated endometriosis daily pain diary (EPDD v3) [12] via an online secure electronic case report form hosted on Castor EDC. This diary will be filled in for 4 weeks and will fulfil two purposes:
Ensure that the participant meets the minimum pain requirements to enter the study andIf the participant is included in the study, this becomes the baseline/pre-treatment data for future analysis.

If eligible based on pain diary scores (averaged across 4 weeks), participants will be required to provide a copy of their most recent laparoscopy report and/or the gynaecologists report/letter that confirms visualisation of endometriosis. This must be within the previous 5 years of their entry into the trial. Upon receipt of the completed EPDD and the proof of surgical confirmation, participants will be included in the study.

### Randomisation

After signing the informed consent document and satisfying the eligibility criteria, participants will be randomised in a 1:1 ratio to either the active treatment group (Gynoclear™) or the placebo control.

Using Castor EDC’s randomisation function, a randomisation sequence using a block size of 6, with 1:1 group allocation, was performed on the 15th of January 2019 by NICMs Clinical Trial Manager who is external to this study. Randomisation numbers were allocated in permuted blocks of 6 containing 3 active and 3 placebo randomisation numbers. The investigator will allocate each randomisation number in order of number sequence starting with the lowest number in each block and using all numbers in a block of 6 before starting with the lowest number in the next block of numbers. As soon as the randomisation number is assigned, it will be recorded on the participant log, in the patient notes and case report form. Details of any patients randomised out of sequence will be notified immediately to the Chief Investigator.

### Blinding

All study teams, participants and data analysts are blind to group allocation. Unblinding of participants to the study’s medical monitor, [name] will be permitted if serious adverse events are reported.

### Study interventions

Production of study supplement for the trial will be from one production batch lot and was manufactured according to Good Medical Practice guidelines. Study supplement dosing is six capsules (active or placebo) per day, taken three times daily, two capsules per time, preferably with food. The placebo matches Gynoclear™ (active) in colour, taste and smell. Table 2 outlines the composition of both the interventional product and placebo.

**Table 2 Tab2:** Composition of interventional product (Gynoclear™)

Active ingredients per capsule (extracts equivalent to)	
*Cinnamomum cassia* twig bark, dry (Cinnamon) 920 mg	
*Poria cocos* fruiting body (Poria) 920 mg	
*Carthamus tinctorius* flower, dry (Safflower) 920 mg	
*Paeonia suffruticosa* root bark, dry (Tree peony) 920 mg	
*Paeonia lactifora* root, dry (Peony) 920 mg	
*Salvia miltiorrhiza* root and rhizome, dry (Red sage) 900 mg	

